### Experimental protocol

Participants attend the outpatient clinics every three months. After informed consent the participants meet fasting at the first visit in the outpatient clinic at 08:00 a.m. Information about demography, lifestyle and clinical characteristics are gathered. Weight and height are measured without shoes. Blood pressure is measured twice after 10 minutes rest in a sitting position. As a measure of peripheral and autonomic neuropathy, biothesiometry, beat-to-beat variation, and orthostatic blood pressure responses are assessed. A 12-lead electrocardiogram is recorded and visually assessed. State of hypoglycaemia awareness is classified by a validated method [27,28]. Patients are asked: “Do you have symptoms when you have a hypo?” The subjects can answer “always” (normal awareness), “usually” (impaired awareness), and “occasionally” or “never” (unawareness). The frequencies of episodes of mild hypoglycaemia per week (defined as manageable by the patient) and severe hypoglycaemia in the previous year are determined on the basis of the aforementioned questionnaires used for screening of patients for the present trial. Recall of severe hypoglycaemia is well preserved during a one-year period [27]. Fasting blood samples are taken and samples for later analyses are centrifuged, processed and stored immediately at −80°C. HbA1c and C-peptide concentrations are measured centrally at Steno Diabetes Center. At the end of visit 1 a 30-min ACTH test (Synacthen®, 0.25 mg i.v.) is performed. After a breakfast in the outpatient clinic the patient’s insulin injection technique is tested and corrected if needed. Three questionnaires about quality of life are filled in. The EuroQol-5 dimension quality of life index (EQ-5D), the Insulin Treatment Satisfaction Questionnaire (ITSQ) and the Hypoglycemia Fear Survey (HFS). EQ-5D is a commonly used, short questionnaire assessing health-related quality of life. Patients describe their health status on five domains (mobility, self-care, usual activities, pain/discomfort, anxiety/depression) with three different answers: “I have no problem”, “some problem”, or “extreme problem”. Furthermore, patients rate health state on a visual analogue scale [29,30]. The ITSQ measures treatment satisfaction concerning the insulin regimen and comprises 22 questions about different aspects of insulin treatment [31]. The HFS comprises 33 questions and measures to what degree patients change daily practise to avoid hypoglycaemia and measures different aspects of worries of episodes of hypoglycaemia [32]. At the end of the visit patients are centrally randomised at Steno Diabetes Center by an assistant not further involved in the trial, based on site-specific computer-generated randomisation lists in blocks of four patients. Finally, free study medication is handed out.

### Endpoint registration

#### Severe hypoglycaemia

In case of a suspected episode of severe hypoglycaemia, patients are instructed to make a telephone call within 24 hours to a call center served by a trained diabetes nurse. The nurse performs a structured interview with the patient to validate the severity (need for assistance from others) and the plausibility of the event according to Whipple’s triad: I) characteristic hypoglycaemic symptoms; II) biochemical confirmation with plasma glucose ≤ 3.9 mmol/l; and III) adequate response to treatment with carbohydrates, glucose or glucagon. According to Whipple’s triad only episodes fulfilling all criteria can be considered definite, whereas those fulfilling two criteria can only be considered probable. Questions about time, place, blood glucose, possible cause(s) of hypoglycaemia, and types of help given to the patient are asked along with questions about health-related quality of life and questions about any consequences of the episode regarding physical or material damage and work-related absenteeism. Furthermore, at every visit to the outpatient clinic patients are asked if they have experienced any episodes of severe hypoglycaemia not recorded by telephone interview. In such cases an interview is carried out by the patient’s doctor or nurse using the same questionnaire as mentioned above. All telephone interviews are done by the same two study nurses (blinded to the treatment modality) located at Hillerød Hospital. Data from the last 9 months of each treatment arm will be used for endpoint analyses.

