## Objective

The primary objective is to evaluate the effect of treatment with insulin analogue and human insulin over the preceding 9 months in each treatment arm on the incidence of severe hypoglycaemia in patients with type 1 diabetes prone to hypoglycaemia.

The secondary objectives are – with reference to the ADA criteria for classification of hypoglycaemia [26] – to evaluate the effects of insulin analogue and human insulin from 3 to 12 months of treatment on the incidence of:

· documented (mild) symptomatic hypoglycaemia.

· asymptomatic hypoglycaemia.

· severe hypoglycaemia, documented symptomatic hypoglycaemia, and asymptomatic hypoglycaemia during daytime.

· severe hypoglycaemia, documented symptomatic hypoglycaemia, and asymptomatic hypoglycaemia during night-time

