## Methods/design

### Design

The study is a Danish two-year, investigator-initiated, prospective, randomised, open, blinded endpoint (PROBE), multicentre, cross-over trial investigating the effect of insulin analogues versus human insulin on the frequency of severe hypoglycaemia (Figure 1). Patients are randomised to treatment with basal-bolus therapy with insulin detemir and insulin aspart (Levemir®/Novorapid®) or human NPH insulin and human regular insulin (Insulatard®/Actrapid®), in random order. Doses of insulin are adjusted according to individual patient need at the discretion of the investigator. Thus, a treat-to-target design is deliberately not used in order not to intervene with present glycaemic control and everyday clinical practice, which otherwise in itself will interfere with the risk of hypoglycaemia. The best obtainable glycaemic control for the individual patient is strived for in both treatment periods. The protocol did not specify the timing and number of insulin injections per day. In general, a four times daily basal-bolus regimen was selected, e.g. basal insulin before bedtime and prandial insulin before meals. Patients were instructed in insulin injection technique at the beginning of each treatment arm. Endpoints are assessed during the last 9 months of each treatment arm, the first 3 months being used for run-in on a new treatment regimen. Optional admissions for overnight plasma glucose measurements followed by three days of blinded continuous glucose monitoring (CGM) are performed after 6 and 12 months of treatment in each treatment arm.

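### The blinded-endpoint label is documented only for telephone interviews; severe episodes first reported at a clinic visit are interviewed by the patient's own doctor or nurse, with no masked grading described

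*Protocol article*

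**What the plan says.** The Design section of the protocol article describes a "randomised, open, blinded endpoint (PROBE), multicentre, cross-over trial". The primary objective concerns the effect of the two insulin regimens "on the incidence of severe hypoglycaemia in patients with type 1 diabetes prone to hypoglycaemia".

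The section on severe hypoglycaemia, under Endpoint registration, gives two routes by which an episode can be recorded.

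- **Telephone route.** After a suspected episode, "patients are instructed to make a telephone call within 24 hours to a call center served by a trained diabetes nurse". The nurse checks severity (whether others had to help) and plausibility against Whipple's triad: symptoms, plasma glucose of 3.9 mmol/l or below, and response to treatment. Three criteria make an episode definite and two make it probable. On blinding, the text says: "All telephone interviews are done by the same two study nurses (blinded to the treatment modality) located at Hillerød Hospital".
- **Clinic route.** At every visit, "patients are asked if they have experienced any episodes of severe hypoglycaemia not recorded by telephone interview". The text continues: "In such cases an interview is carried out by the patient’s doctor or nurse using the same questionnaire".

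The section ends by assigning the data from the last 9 months of each arm to the endpoint analysis, without distinguishing the routes. The Design section leaves insulin dosing to the investigator. The Experimental protocol section sets visits three months apart.

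**The concern.** The design label covers the endpoint as a whole, while the statement on who is blinded covers one of its two sources. On the other source the interviewer belongs to the team treating the patient with a known insulin. Whether others' help was really needed, whether symptoms were characteristic and whether the response to treatment was adequate all leave some room for judgement. If knowledge of the insulin shifts those judgements differently in the two treatment periods, the shift acts directly on the primary rate ratio.

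In an open trial with a patient-reported event, masked assessment is the safeguard that the PROBE label promises. A reader of the results would assume that it applied to every counted episode.

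**Working it through.** **1. The two routes side by side**

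| | Telephone | Clinic visit |
|---|---|---|
| Interviewer | One of two study nurses | Patient's own doctor or nurse |
| Blinding stated | Yes | No |
| Delay | Instructed within 24 hours | Up to about 3 months (visit interval) |
| Questionnaire | Structured | The same one |
| Later masked grading | Not needed | None described |
| Enters endpoint analysis | Yes | Yes; no separation stated |

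The document never calls the clinic interviewers unblinded. That they know the insulin is an inference from open treatment, dosing by the investigator, and a blinding statement limited to telephone interviews.

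**2. The plan's own figure**

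Inputs from the Power calculation section: rate ratio 0.85, power 80%, test level 5%, 1220 events, exact binomial test of 1/2. The alternative is P = 1/(1 + 0.85) = 0.5405. With 0.025 in each tail and 1220 events, the test rejects at 645 or more events on one treatment. Actual type I error is 0.048 and power is 0.805, so the stated 1220 reproduces. It serves here as the yardstick.

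**3. How large could the bias be?**

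The document gives neither of the two inputs needed. Both are assumptions:

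- u = share of episodes that arrive by the clinic route;
- d = extra proportion of those episodes not accepted in one arm because the interviewer knows the insulin.

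With no true difference, the apparent rate ratio is 1 − u × d. Putting p = 1/(1 + ratio) into the same exact test, with 1220 events held fixed, gives the chance of a significant result in either direction.

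| u | d | Apparent ratio | Type I error | Shift as share of the 15% target |
|---|---|---|---|---|
| 5% | 10% | 0.995 | 0.049 | 0.5/15 = 3% |
| 5% | 20% | 0.99 | 0.052 | 1/15 = 7% |
| 10% | 20% | 0.98 | 0.062 | 2/15 = 13% |
| 20% | 20% | 0.96 | 0.107 | 4/15 = 27% |
| 30% | 20% | 0.94 | 0.186 | 6/15 = 40% |

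The bias could equally favour human insulin. At u = 20% and d = 20%, with the losses in the human-insulin arm, a true ratio of 0.85 would appear as 0.85/0.96 = 0.885, and power would fall from 0.805 to 0.56.

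**The case against.** The case on the other side has weight on six points.

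- **Who grades.** A reader might infer that clinic staff decide alone, unblinded, which late-reported episodes count. The text does not say this. It says that they conduct the interview, not who assigns final status, and a masked grading step could stand in a full protocol that is not shown. What remains is that the article names who is blinded, limits this to one route, gives the other route to someone else, and still applies the blinded-endpoint label to the whole.
- **Definite versus probable.** A reader might also infer that grading an episode down to probable removes it from the primary count. The document states no such exclusion. If both grades count, bias could enter only through the judgement of needed assistance or through a failure to meet two criteria.
- **Other safeguards.** Masked interviewing is not the trial's only protection. There is a fixed definition, a numerical glucose threshold, one structured questionnaire for both routes, and a within-patient comparison. These narrow the room for assessor bias without closing it.
- **Recall.** The Experimental protocol section says that recall of severe hypoglycaemia holds up over a year. This answers the worry about forgetting, but not the one about an interviewer who knows the insulin.
- **Patients are unblinded on both routes.** This is true. Masking the interviewer removes assessor bias only, and a telephone-only analysis is not a bias-free benchmark.
- **Timing.** The Timeline section puts the last visit in November 2011, so the clinic procedure can no longer be changed. This limits the remedy to what can be done with completed forms.

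**Conclusion.** The point holds as a mismatch between label and procedure. Blinding is documented for telephone interviews only. Clinic-reported episodes are interviewed by staff who can be presumed to know the insulin, and no masked grading is described before they join the primary count.

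The size is unknown. Assuming about 20% differential acceptance, the effect is negligible if about 5% of episodes take the clinic route. It may be material against a 15% target if 20–30% or more do. The document gives no direction for the bias, and neither a large bias nor an invalid primary result can be claimed from it. The point merits correction because the remedy is cheap. The sample size calculation is not affected.

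**What to change.** Before analysis:

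1. Have the same two blinded nurses re-grade the completed clinic-route questionnaires with insulin names masked, using the same severity and Whipple criteria, and use these grades in the primary count.
2. Report the number of episodes by route and by treatment, so that readers can judge how much of the endpoint is concerned.
3. Add a sensitivity analysis limited to telephone-validated episodes, noting that it still depends on unblinded patients choosing to phone.

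If masked grading already takes place, one sentence saying so settles the main point. If it does not and cannot be done, restrict the blinded-endpoint claim to telephone-reported episodes.

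The cost is a little extra time for two nurses already in the trial, and one further analysis. The limitation is that masked re-grading cannot undo any influence on how clinic staff wrote down the answers.

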#### Mild symptomatic and asymptomatic hypoglycaemia

Patients are instructed and strongly encouraged to make a 7-point self-monitored blood glucose (SMBG) profile two days a week in the entire study period. All values are entered into a diary with study-specific guidance and at every outpatient visit the diary is evaluated by the investigator and copies of the relevant pages are saved as source data. If patients measure a SMBG value ≤ 3.9 mmol/l, they are instructed to write down if they have concomitant symptoms of hypoglycaemia. All SMBG values are measured with the Ascensia® CONTOUR® blood glucose monitoring system (Bayer Health Care, Leverkusen, Germany).

#### Nocturnal hypoglycaemia

Patients are instructed to measure a nocturnal blood glucose once every month at 3 a.m. Moreover, patients are invited (optional) to stay overnight at Steno Diabetes Center four times during the study (two times at month 6 and 12 in every treatment arm). In the evening before bedtime, a study-specific blinded continuous glucose monitoring (CGM) device (Guardian® REAL-time (with a “black” display), Medtronic Minimed, Northridge, USA) is mounted by a trained study nurse and the patient is instructed how to calibrate the device, using capillary glucose measurements. Thereafter, a venous line is inserted in an anticubital vein. During the night, blinded samples for subsequent plasma glucose measurements are drawn once every hour, while the patient is sleeping.

#### CGM

Interstitial glucose concentrations are assessed for three days in patients who accept the four optional overnight stays at Steno Diabetes Center, i.e. 12 days of CGM in total. After the three days the glucose sensor and monitor are collected and data are downloaded to a computer for further analysis. These data remain blinded until the end of the study and are not used to control glycaemic levels during the study period. Special blinded versions of the CGM device with a “black screen” were supplied by the manufacturer. The CGM data will provide a unique possibility to assess the accuracy of CGM and compare time spent at hypoglycaemia, number of unrecognized episodes of hypoglycemia in this selected patient population.

#### HbA1c and plasma glucose

At every visit to the outpatient clinic (totalling 9 visits per patient) blood samples are drawn to measure HbA1c levels (analysed centrally at Steno Diabetes Center) and random plasma glucose concentrations (measured locally).

### Power calculation

In the power calculation, the number of events in each treatment period is assumed to be distributed according to a Poisson model. No period effect exceeding the 3 months of run-in is assumed. Based on the total number of observed events for each individual patient, the number of events for a treatment period is reduced to a binomial distribution:

Binomial (total number of events, λ_human insulin_/(λ_human insulin_ + λ_insulin analogue_)), which under the null hypothesis of no difference in event rate between insulin analogues and human insulin becomes binomial (total number of events, ½). The power calculations are thus performed with the use of an exact test of number of events in a binomial distribution with the probability of p = 1/2 versus alternatively with the probability of P = λ_human insulin_/(λ_human insulin_ + λ_insulin analogue_) = 1/(1+ λ_insulin analogue_/λ_human insulin_). The sample size calculation thus indicates the total number of events needed. The study population is selected to be patients with an expected increased risk of severe hypoglycaemia. Assuming an incidence of 2.8 severe hypoglycaemic events per patient-year, corresponding to 2.09 per 9 months treatment period, and setting minimal relevant difference (MIREDIF) to a reduction in the incidence of severe hypoglycaemia of 15% (based on the conclusion of the American Diabetes Association Workgroup on Hypoglycemia ”that any significant reduction in severe hypoglycemia (that requiring the assistance of another individual), even by as little as 10–20%, would be advantageous” [26]), this will correspond to a reduction in the relation between human and analogue insulin of: λinsulin analogue/λhuman insulin = 0.85. Setting power to 80% and a test level of 5%, the total number of events needs to be 1220. With an expected number of events of 2.09 + 1.75 (1.75 = 2.09 x 15% reduction in incidence of severe hypoglycaemia) = 3.84 events per 18 months’ treatment, this corresponds to a need for 315 patients. With an expected dropout rate of 15%, 370 patients need to be included.

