## Background

Severe hypoglycaemia still represents a significant risk for many patients with type 1 diabetes. The condition is feared by patients [1,2] and relatives [3] and remains a major barrier in achieving recommended glycaemic targets [4]. Moreover, severe hypoglycaemia may, although rarely, lead to permanent brain damage or death [5]. The frequency of severe hypoglycaemia in type 1 diabetic populations is 1–1.7 episodes per patient-year [6-14]. The distribution of episodes is, however, very skewed. Thus, 20% of patients with type 1 diabetes experience two or more episodes of severe hypoglycaemia per year [15]. Once prone to recurrent severe hypoglycaemia, patients often remain so throughout their life.

Insulin analogues were developed to improve treatment of insulin-treated diabetes with respect to glycaemic control and avoidance of hypoglycaemic episodes. Short-acting insulin analogues (aspart, lispro and glulisine) were designed to mimic the fast physiological postprandial insulin release and long-acting insulin analogues (detemir and glargine) were designed to mimic the basal continuous insulin release with minimal peak action, thereby leading to a presumed decreased risk of hypoglycaemia. The effect of insulin analogues on glycaemic control has been documented in large trials [16,17]. However, for several reasons the impact of insulin analogues on the frequency of severe hypoglycaemia is less clear. Firstly, most studies comparing the effects of human insulin with those of insulin analogues specifically exclude patients at risk of severe hypoglycaemia, such as patients with previous severe events or impaired hypoglycaemia awareness, from participation [18-21]. This renders the trials insufficiently statistically powered to detect differences in the frequency of severe hypoglycaemia and the conclusions from these studies can not readily be extrapolated to patient groups prone to severe hypoglycaemia. Secondly, hypoglycaemia is often less well defined and detected, at best as a secondary endpoint, with reports including a mixture of mild, severe, and asymptomatic hypoglycaemia. Thirdly, severe hypoglycaemia should be analysed according to a statistic model that takes into account the much skewed distribution of episodes e.g. negative binomial or zero-inflated models [22].

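### The 80% power at 1220 events is a best case: it allows for no within-patient overdispersion and does not match the negative binomial option in the analysis plan

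*Protocol article*

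**What the plan says.** The Power calculation section of the protocol article makes three assumptions.

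- On the counts: "the number of events in each treatment period is assumed to be distributed according to a Poisson model".
- On time: "No period effect exceeding the 3 months of run-in is assumed".
- On the effect: one rate ratio, analogue to human insulin, of 0.85.

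It then removes the patient's own rate: "Based on the total number of observed events for each individual patient, the number of events for a treatment period is reduced to a binomial". The test is an "exact test of number of events in a binomial distribution with the probability of p = 1/2" against 1/(1 + 0.85). The result is: "Setting power to 80% and a test level of 5%, the total number of events needs to be 1220". Dividing by 3.84 expected events per patient gives 315 patients, or 370 with 15% dropout.

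Two other sections bear on this. The Background says that "severe hypoglycaemia should be analysed according to a statistic model that takes into account the much skewed distribution of episodes", and names negative binomial and zero-inflated models as examples. The Statistics section allows either a negative binomial or a Poisson model with a log link. It lists treatment, period, HbA1c and several patient characteristics as terms. It also assumes that a patient's status is the same in both periods, and relies on the long follow-up to even out good and bad spells.

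**The concern.** The pooled binomial test treats the 1220 events as independent trials with one success probability. Conditioning on the patient's total justifies this only if, given the patient, counts in each period are Poisson and the rate ratio is about the same for everyone. If episodes cluster in bad spells, or some patients benefit much more than others, the split of events between periods varies more than a binomial allows. Patients with many episodes then carry less information than their event count suggests.

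The planned analysis may also be a different procedure from the one that was powered. A negative binomial regression without a patient term treats a patient's two periods as unrelated, and so gives up the within-patient comparison for which the crossover was chosen.

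At stake is how a non-significant result is read. The protocol takes a 15% reduction as the smallest relevant one and links the question to the higher cost of analogues. A null result set against a claimed 80% power could be taken as evidence of no relevant difference when the real power was well below that.

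**Working it through.** **Inputs.** From the Power calculation section: "Assuming an incidence of 2.8 severe hypoglycaemic events per patient-year, corresponding to 2.09 per 9 months treatment period"; rate ratio 0.85; 5% level; 80% power; 1220 events; 3.84 events per patient; 315 evaluable patients. Sidedness is not stated. Within-patient dispersion, between-patient variance and spread of the treatment effect are not given, so the values below are assumptions.

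**1. The plan's figure.** p1 = 1/1.85 = 0.5405. With 1220 events, the exact two-sided test rejects in favour of analogues at 645 or more events on human insulin (upper-tail probability 0.0241 under p = 1/2). Power under p1 is 0.805. A one-sided test would need only about 950 to 980 events, so the figure is two-sided. The stated 1220 reproduces.

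Small side differences: 2.09 × 0.85 = 1.78 (stated 1.75), and 1220/3.84 = 317.7 (stated 315). With the unrounded sum 2.09 × 1.85 = 3.8665, 1220/3.8665 = 315.5. None of this affects the point.

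**2. Does skew between patients matter?** Simulation with 315 patients, 4000 runs per setting, gamma-distributed patient rates and Poisson counts within each patient-period. At between-patient variance 0, 1, 2 and 4, power of the exact test stays at 79 to 80% and type I error at about 5%. Skew alone does not reduce the planned power.

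**3. Overdispersion within patients.** Let φ multiply the variance of the within-patient split. The 1220 events divide as 659 and 561 (1220 × 0.5405 and the rest), so

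power = Φ( |ln 0.85| / √(φ × (1/659 + 1/561)) − 1.96 ), with |ln 0.85| = 0.1625 and √(1/659 + 1/561) = 0.0574.

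Events needed are 1220 × φ, and evaluable patients are that number divided by 3.84. The last column is the type I error of the plain binomial test if it is kept, 2 × (1 − Φ(1.96/√φ)).

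| Assumed φ | Power at 1220 events | Events for 80% | Evaluable patients | Type I error, plain test |
|---|---|---|---|---|
| 1 | 81% | 1220 | 318 | 5% |
| 1.25 | 72% | 1525 | 398 | 8% |
| 1.5 | 64% | 1830 | 477 | 11% |
| 2 | 52% | 2440 | 636 | 17% |
| 3 | 37% | 3660 | 954 | 26% |

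Solving the same formula for the ratio that gives 80% power at 1220 events, the detectable reduction is about 15%, 16%, 18%, 20% and 24%.

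The simulation agrees. With a patient-by-period variance of 0.1 and a patient-clustered variance in the test, power is 74%, 67%, 63% and 54% at between-patient variance 0, 1, 2 and 4. Skew between patients is harmless alone but enlarges the loss once there is any within-patient excess.

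**4. Varying treatment effect, no other excess.** With a log-scale standard deviation of 0.25, power is 80% (no skew) and 74% (between-patient variance 2). With 0.5 it is 72% and 59%. A small spread costs little.

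**5. Negative binomial model with only the listed terms.** Suppose counts are Poisson given the patient, with between-patient variance k left over after the covariates. With 1/2.09 + 1/1.7765 = 1.0414:

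- standard error that the model reports: √((1.0414 + 2k)/315)
- actual standard error, since the patient's rate cancels in the comparison: √(1.0414/315) = 0.0575
- power ≈ Φ( (0.1625 − 1.96 × reported) / 0.0575 )

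| Assumed k | Reported SE | Power, formula | Power, models fitted to simulated data |
|---|---|---|---|
| 0.25 | 0.0700 | 67% | about 65% |
| 0.5 | 0.0805 | 53% | about 53% |
| 1 | 0.0983 | 30% | about 30% |

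Here the test is conservative rather than too liberal: it charges the treatment comparison with variance that the crossover has removed.

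**The case against.** A reader might infer that the document contradicts itself, because the Background calls the distribution very skewed while the sample size is Poisson. The documents do not support this. The Background explains the skew as a difference between patients: a fifth of them have two or more episodes a year. A negative binomial distribution across patients is compatible with Poisson counts around each patient's own stable rate, and conditioning on the total is a legitimate way to deal with that skew. The Statistics section's assumption of unchanged status across periods fits the same picture. This objection stands in full.

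Nor can it be stated as fact that the trial lacks power under its own analysis model. The Statistics section permits Poisson as well as negative binomial, no passage asserts within-patient overdispersion or a varying effect, and the remark on good and bad periods only hints at the former. The Poisson assumption is openly stated, and every loss shown above rests on assumed values. A patient term may be specified in the full plan, which is not shown. This also stands, and so the point is put conditionally.

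Finally, the last visit was in November 2011, so the sample size cannot be changed, and reporting a confidence interval is a partial safeguard against misreading a null result. That limits the remedy to the stated claim and the analysis model. It does not make the unconditional 80% right, and choosing a model that keeps the within-patient comparison still affects the result.

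**Conclusion.** The point holds in a limited form. The 80% is correct for an exact binomial test conditional on each patient's total, with Poisson counts within patient-period and a broadly common rate ratio of 0.85. It is a best case, because departures from these conditions lower power and none is allowed for. At an assumed within-patient dispersion of 1.5 power is about 64%, and at 2 about 52%. At 2 the detectable reduction, about 20%, lies at the upper end of the 10 to 20% range that the protocol cites to justify its 15%.

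Separately, the test that was powered is not the negative binomial option in the Statistics section. If that model has no patient term, between-patient skew alone would bring power to about 65%, 53% and 30% at assumed variances of 0.25, 0.5 and 1. The direction of these effects is certain. Their size is not, since the documents give neither the dispersion nor the between-patient variance.

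**What to change.** 1. Restate the claim in the Power calculation section: 80% power if counts are Poisson within patient-period and the analysis conditions on or models the patient. Add power by dispersion factor, and note that the events needed are 1220 times the factor.
2. Estimate the dispersion once from counts blinded to treatment, and report the reduction detectable at the achieved sample.
3. Align the Statistics section with the power calculation: state that the Poisson or negative binomial model conditions on the patient or includes a patient term. If a Poisson or binomial form is used, let its variance allow for within-patient overdispersion, to protect the type I error.

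The cost is a few sentences and a small table. No extra patients or data are needed. The stated power becomes less favourable.
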